### Study population

The study will enrol adult patients (> 18 years old) diagnosed with acute COVID-19 disease between 01/03/2020 and 01/02/2025 at the participating centres. The COVID-19 patients will be divided into two groups: Group 1 (hospitalised) and Group 2 (outpatients).

Inclusion criteria for the study require a confirmed diagnosis of SARS-CoV-2 infection based on a positive SARS-CoV-2 RNA test on nasopharyngeal swab or other respiratory samples. Mild COVID-19 disease is defined as cases without hospital admission, while moderate/severe disease includes cases requiring hospitalisation for COVID-19 or hospitalisation for other medical issues with a positive SARS-CoV-2 RNA sample. Patients must provide informed consent for the study to be eligible for inclusion.

Exclusion criteria include death during hospitalisation and patient refusal to participate.

The study will also enrol a control group of hospitalised patients for respiratory infections other than COVID-19 disease during the same study period, with enrolment occurring at hospital discharge and follow-up appointments scheduled at the post COVID clinic with the same timing as COVID-19 patients. These patients will be enrolled if they are adults hospitalised for respiratory infections requiring any type of oxygen therapy or Intensive Care admission (Fig. 1).

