## Introduction

The coronavirus disease 2019 (COVID-19) pandemic has caused widespread morbidity and mortality worldwide, with over 5 million deaths attributed to the acute syndrome caused by the severe acute respiratory syndrome coronavirus 2 (SARS-CoV-2) virus [1].

However, the long-term consequences of COVID-19, also known as post-acute sequelae of COVID-19 (PASC) or long-COVID, are also concerning [2–4]. These long-lasting symptoms may include fatigue, muscle weakness, shortness of breath, cough, joint pain, chest pain, anosmia or dysgeusia, cognitive dysfunctions, sleep disorders, anxiety and depression. These symptoms may be new, following initial recovery from the acute COVID-19 illness, or may persist from the beginning of the disease. In October 2021, the World Health Organization (WHO) identified the “post COVID-19 condition” as the presence of symptoms usually three months after the onset of COVID-19 that last for at least two months and cannot be explained by a different diagnosis. Patients may also be diagnosed with residual organ damage after acute COVID-19, particularly in the lungs, heart, central nervous system, and peripheral nervous system.

Preliminary data have shown a high prevalence of post-COVID-19 condition, although there is considerable variation among different studies. This variation can be attributed to the utilisation of different definitions for post-COVID-19 condition, inclusion of diverse populations, and the use of varying or non-standardised methods to assess the persistence of symptoms.

A recent systematic review of 20 observational studies, comprising 5,440 enrolled patients, reported a prevalence of post-COVID-19 condition between 4.7% to 80% [5]. Several studies have demonstrated high rates of ongoing symptoms after hospital discharge for acute COVID-19 illness (87% after two months and 70% after six months) and in outpatient COVID-19 subjects (32% at 30–45 days from the acute episode) [6–8]. A systematic review of 57 studies, comprising more than 250,000 patients recovered from COVID-19, showed that 54% of patients reported at least one post-acute sequelae at one month (short-term), 55% at 2–5 months (intermediate term), and 54% at 6 or more months (long-term) [9].

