### Study design

This is an observational retrospective and prospective, multicentre, cohort study. The study will last for 3 years, from February 2022 to February 2025.

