### Patient assessment and follow-up protocol

The patient assessment and follow-up protocol for acute COVID-19 disease involves follow-up visits at 2–3, 6–9, and 12–15 months after clinical recovery. At each visit, routine blood exams and medical visits will be conducted, along with several assessments via questionnaires, including the short version of the post COVID-19 WHO Case Report Form (WHO CRF) for collection of symptoms and newly emerged complaints after COVID-19, the Fatigue Numerical Rating Scale, the Medical Research Council (MRC) dyspnoea scale, the 5-level EQ-5D test (EQ5D-5L), the 12-item WHO Disability Assessment Schedule (WHODAS), the Montreal Cognitive Assessment (MOCA), the Hospital Anxiety and Depression Scale (HADS-A/D), and a screening tool named PCL-5 for Post-Traumatic Stress Disorder (PTSD). If patients are unable to attend the post-COVID-19 clinic, the questionnaires will be able to be completed through a phone interview. All questionnaires will be standardized and available in multiple languages (Fig. 1).

Further instrumental diagnostic evaluations such as diffusing capacity of lung carbon monoxide (DLCO), spirometry, lung computed tomography (CT) scans, pneumological evaluation, echocardiography, cardiological evaluation, neurological evaluation, rehabilitation medicine specialist examination, and psychological evaluation will be conducted as necessary.

Pulmonary symptoms are common after the acute phase, thus patients undergo the MRC dyspnoea scale and oxygen saturation measurement at each post-COVID visit. Further evaluations such as chest CT scans, diffusing capacity of lung carbon monoxide (DLCO), spirometry, and a complete pneumological evaluation will be performed if oxygen saturation is < 95% or MRC dyspnoea scale grade is 2–5.

Patients who recovered from acute COVID-19 disease could present a higher risk of cardiac diseases, including heart failure, myocardial infarction, and arrhythmia in the mid- and long-term [18]. During the scheduled post-COVID visits, patients undergo a complete medical examination, including heart rate and blood pressure measurement, and fill in the MRC dyspnoea scale. Further evaluations such as an electrocardiogram, a cardiologic visit, and an echocardiography will be performed as necessary.

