Neurocognitive and neuropsychiatric sequelae are important to investigate for their great impact on patients’ quality of life [6, 19, 20]. Neurocognitive and neuropsychological performance will be assessed by questionnaires, including the previously mentioned HADS-A/D, PCL-5, and MOCA, which will be performed at each scheduled visit. Patients will be referred to a psychologist or a neurologist as necessary (Table 1).

**Table 1 Tab1:** Displaying the specific assessments to be conducted at each study time point

Study Flowchart				
**Procedures**	**At acute phase**	**At T1 (2–3 months)**	**At T2 (6–9 months)**	**At T3 (12–15 months)**
Nasopharyngeal swab	X			
Demographic/clinical data collection	X			
Routine blood tests		X	X	X
Blood/serum samples collection		X	X	X
Medical visit, oxygen saturation (SO2) measurement		X	X	X
Symptoms assessment (WHO CRF)		X	X	X
Fatigue Numerical Rating and Severity Scale		X	X	X
Modified MRC Dyspnoea Scale		X	X	X
Hospital re-admission, relapse or new comorbidity		X	X	X
COVID-19 vaccination status		X	X	X
QoL (EQ5D-5L)		X	X	X
Montreal Cognitive Assessment (MOCA)		X	X	X
Psychological questionnaires (HADS-A/D, PCL-5)		X	X	X
WHODAS questionnaire		X	X	X
If abnormal SO2, DLCO		X		X
If abnormal SO2, spirometry		X		X
If abnormal SO2 and/or clinically indicated, pneumology visit		X	X	X
Electrocardiogram (ECG)		X		
If cardiac symptoms, echocardiogram		X		X
If cardiac symptom and/or clinically indicated, cardiology visit		X	X	X
If abnormal psychological questionnaires and/or clinically indicated, psychology evaluation		X	X	X
If abnormally MOCA and/or clinically indicated, neurology visit		X	X	X
If abnormally WHODAS and/or clinically indicated, rehabilitation medicine visit		X	X	X

Legend: T1, T2 and T3: post COVID-19 visit at 2-3 months, 6-9 months and 12-15 months after clinical recovery.

Blood/serum samples collection: whole blood samples will be stored, centrifuged, and separated into plasma and peripheral blood mononuclear cells for immunological and viral analyses

WHO CRF, WHO’s Post COVID case report form; MRC dyspnoea scale, Modified Medical Research Council Dyspnoea Scale; QoL (EQ5D-5L), quality of life (5-level EQ-5D version); MOCA, Montreal Cognitive Assessment; HADS-A/D, Hospital Anxiety and Depression Scale; PCL-5, Post Traumatic Stress Disorders (PTSD) checklist for DSM-5; WHODAS, World Health Organization Disability Assessment schedule 2.0, 12-item version; DLCO, Diffusing capacity of the lung for carbon monoxide test

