The sample size calculation will be determined by the number of expected events in the follow-up period. Based on the currently available data, we estimated an incidence of WHO post COVID-19 condition of 54% (95%CI 45–69%). We will use the comparison between the risk of developing post-COVID-19 condition in participants infected with the Delta versus Omicron viral variant of concern (VoC) for the sample size calculation. According to recent analysis, after controlling for vaccination and other confounders, the risk of hospitalisation comparing Omicron versus Delta variant ranged between 0.55 and 0.88 [21]. Our assumption is that if post COVID-19 condition occurs due to the direct effects of the virus (e.g., through disease severity, level of hyper-inflammation, or other), a similar difference could be seen when comparing the long-term risk of developing post COVID-19 condition by VoC. The cohort of 2,300 participants, accounting for 35% of follow-up, will still guarantee 90% power to detect a reduction in the risk of post-acute sequelae of at least 25% comparing participants infected with Omicron vs. Delta variants.

Data handling and statistical analyses will be performed by the team of statisticians and Artificial Intelligence experts in WP5. Python computing will be used for executing the statistical analysis.

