## Possible study strengths and limitations

The strengths of this medical study include its international cohort of patients who will be followed-up for one year after acute infection. The study also collects a comprehensive list of symptoms and objective measures of symptoms, such as dyspnoea, fatigue, and psychological issues, through standardised questionnaires and scales. Additionally, blood samples will be collected during the acute phase and follow-up for future studies on possible pathogenetic mechanisms of post COVID-19 condition.

However, there are also some potential limitations of the study to consider. One possible limitation is the risk of selection bias, as patients without ongoing symptoms may not keep follow-up appointments, leading to losses in follow-up, despite some statistical methods could be used to handle this bias. Another possible limitation is the potential overestimation of post COVID-19 condition due to the WHO definition, which includes any kind of symptom.

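### The last eligible diagnosis date, the February 2025 study end and the visit schedule cannot all hold; the latest patients cannot reach T1, and the larger gap is at T2 and T3

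*Protocol article*

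**What the plan says.** Four statements in the protocol article bear on this.

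- *Study population*: cases are patients "diagnosed with acute COVID-19 disease between 01/03/2020 and 01/02/2025 at the participating centres". Controls are enrolled over the same period and seen with the same timing.
- *Study design*: "The study will last for 3 years, from February 2022 to February 2025".
- *Patient assessment and follow-up protocol*: "follow-up visits at 2–3, 6–9, and 12–15 months after clinical recovery". The legend to Table 1 repeats this: "T1, T2 and T3: post COVID-19 visit at 2-3 months, 6-9 months and 12-15 months after clinical recovery".
- *Possible study strengths and limitations*: the study is described as an "international cohort of patients who will be followed-up for one year after acute infection".

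*Data analysis* attributes missed post-COVID visits to losses to follow-up. For hospitalised patients only, it proposes inverse probability weights, 1/PS, where PS is the modelled probability of being included in the post-COVID cohort. The text shown gives no follow-up period after February 2025 and no earlier cut-off for any of the three visits.

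**The concern.** Diagnosis stays open until the month in which the study closes, while the schedule needs up to 15 months after recovery. The latest eligible patients therefore cannot have any planned visit, and a wider band of late patients cannot have T2 or T3.

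Three things are at stake.

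1. **Outcome.** The *Introduction* gives the WHO condition as the "presence of symptoms usually three months after the onset of COVID-19 that last for at least two months". Patients diagnosed in the last weeks cannot be observed long enough to meet or fail that definition. The objectives on long-term organ impairment and on the course of symptoms lean on T2 and T3, where the gap is larger.
2. **Comparability over time.** Whether a visit can happen depends on the diagnosis date. The *Discussion* intends to compare pandemic waves, and the sample size rests on the "risk of developing post-COVID-19 condition in participants infected with the Delta versus Omicron viral variant of concern (VoC) for the sample size calculation". Both are linked to date.
3. **Weighting.** If patients whose visit falls after closure are entered as non-attenders, their true probability of attending is zero. Weights of 1/PS then have nobody comparable to up-weight.

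**Working it through.** **Inputs.** Diagnosis window 01/03/2020 to 01/02/2025, 1,798 days (*Study population*). Study end February 2025, read as late as possible, 28/02/2025 (*Study design*). Visit windows 2–3, 6–9 and 12–15 months after recovery (*Patient assessment and follow-up protocol*). Time from diagnosis to recovery is not given; I assume 0 days, which favours the plan, and check 28 days.

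**Step 1: the last eligible patient.** Visit date = diagnosis date + recovery lag + months to visit. For a diagnosis on 01/02/2025 with no lag:

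- T1: 01/04/2025 to 01/05/2025
- T2: 01/08/2025 to 01/11/2025
- T3: 01/02/2026 to 01/05/2026

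All fall after closure. With a 28-day lag, T1 opens on 01/05/2025 and T3 closes on 01/06/2026.

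**Step 2: last diagnosis date that works for each visit.** Last date = 28/02/2025 − months − lag. The window opens in time if the lower limit is subtracted (2, 6, 12 months) and fits completely if the upper limit is subtracted (3, 9, 15 months). Share affected = (01/02/2025 − last date) / 1,798 days. The dates and shares below use no lag.

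| Visit | Last date, window opens | Never opens | Last date, window complete | Incomplete or never opens |
|---|---|---|---|---|
| T1 | 28/12/2024 | 35/1,798 = 1.9% | 28/11/2024 | 65/1,798 = 3.6% |
| T2 | 28/08/2024 | 157/1,798 = 8.7% | 28/05/2024 | 249/1,798 = 13.8% |
| T3 | 28/02/2024 | 339/1,798 = 18.9% | 28/11/2023 | 431/1,798 = 24.0% |

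A 28-day lag moves the opening limits to 30/11/2024, 31/07/2024 and 31/01/2024. Counting only diagnoses from 01/02/2022 (1,096 days), the never-opens shares are 35/1,096 = 3.2%, 157/1,096 = 14.3% and 339/1,096 = 30.9%.

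These are shares of calendar time. Accrual by date is not given, so they cannot be turned into shares of patients.

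**Step 3: weighting.** For a patient whose window opens after closure, P(visit) = 0 and 1/P is undefined. If diagnosis date is left out of the attendance model, the fitted probability is positive, but earlier patients are made to stand in for later ones. If it is included, there is no attender at those dates to carry the weight. Neither recovers the missing outcomes.

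**Step 4: power.** The plan states 90% power for a 25% reduction with 2,300 participants and a 35% follow-up allowance. From 54%, a 25% reduction gives 0.75 × 54% = 40.5%. With two-sided alpha of 0.05 (assumed), 90% power needs 286 per arm. The wording leaves open whether 35% is lost (0.65 × 2,300 = 1,495) or retained (0.35 × 2,300 = 805). At an even split, power is 99.95% or 97.1%. A value near 90% appears at 1,495 if Omicron is about 11% of the cohort (90.8%), but no split is stated, so the 90% is neither confirmed nor refuted.

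At 1,495 and an even split, losing 20%, 40% or 60% of the Omicron arm leaves power of 99.9%, 99.5% and 97.8%. The margin would be thinner if Omicron were a small minority: at a fixed 1,495, power is 90.8% with an 11% share (about 164 patients) and 85.3% with a 9% share (about 135).

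**The case against.** The strongest reply is that the contradiction is narrow and its harm is not documented. Several parts of it stand.

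- **Denominators.** A reader might infer that unseen patients will be counted as lost, or will sit in the incidence denominator without being able to become cases. The article says neither. Its weighted regression runs on those sampled for the visit, so a patient never seen may simply be absent. Such rules are commonly left to a full protocol or SAP, and their absence here is no fault.
- **Variant.** A reader might infer that the missingness falls only on patients with the newest variant and so biases the Delta–Omicron contrast. Late controls are truncated too, and no variant calendar is given. The link to variant is inferred from date order, and many Omicron patients may be unaffected. Bias would need late patients to differ from earlier ones with the same variant, or to be wrongly counted. Variant is also a secondary objective, although it drives the sample size.
- **Size.** A reader might take the 24.0% at T3 as a loss of a quarter of the patients. It is calendar time and demands the whole window. T1 is the visit nearest the three-month definition, and there the figures are 1.9% to 3.6%. The *Discussion* notes falling incidence in Europe, so the share of patients may be smaller.
- **Figure 1.** The timeline figure is not shown and might say that February 2025 closes enrolment rather than follow-up.

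What does not stand is the suggestion that an analysis plan settles the matter. It can define denominators, but it cannot create visits after the study has ended. *Study design* gives the duration of the study, not of enrolment; if follow-up is meant to continue, the text should say so.

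**Conclusion.** The point holds as a conflict between stated dates. With any recovery lag, the diagnosis window, the study end and the visit schedule are incompatible for the latest patients, and the one-year follow-up claim cannot apply to everyone declared eligible. The effect is small at T1 and material at T2 and T3, in the calendar shares given above. Those shares assume closure on 28/02/2025 and no recovery lag, both of which favour the plan.

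The truncation is determined by diagnosis date, in cases and controls alike, and is therefore tied to calendar time and probably to wave and variant. Its consequence is late outcomes that cannot be observed, with a risk of bias if the affected patients are handled as ordinary non-attenders. It is not a power problem at an even variant split. The documents do not support the stronger claims that only newest-variant patients are affected, that the patients will be miscounted, or that the variant contrast is biased.

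**What to change.** Reconcile *Study design*, *Study population* and *Patient assessment and follow-up protocol*. Which statement changes is for the sponsor. Two routes would work.

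1. **State that follow-up continues past February 2025.** For the last cases to complete T3, this means about mid-2026 (01/05/2026 with no recovery lag, 01/06/2026 with 28 days). The cost is a later data lock.
2. **Keep the February 2025 end and set a last eligible date for each visit**, based on when its window opens before closure and expressed as a recovery date, since that starts the visit clock. With closure on 28/02/2025 these are 28/12/2024 (T1), 28/08/2024 (T2) and 28/02/2024 (T3). Requiring the full window to elapse would discard valid visits: a patient who recovered in mid-January 2024 can be seen at 12–13 months. Class later patients as administratively not due, outside that visit's denominator, the non-attender group in the weighting and the 35% follow-up allowance. Limit the one-year claim to patients who could reach T3. The cost is a few sentences and slightly smaller T2 and T3 denominators.

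Under either route, apply the same rule to controls.

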**Fig. 1 Fig1:**
[figure not shown]
Depicting the study population and timeline

### Patient assessment and follow-up protocol

The patient assessment and follow-up protocol for acute COVID-19 disease involves follow-up visits at 2–3, 6–9, and 12–15 months after clinical recovery. At each visit, routine blood exams and medical visits will be conducted, along with several assessments via questionnaires, including the short version of the post COVID-19 WHO Case Report Form (WHO CRF) for collection of symptoms and newly emerged complaints after COVID-19, the Fatigue Numerical Rating Scale, the Medical Research Council (MRC) dyspnoea scale, the 5-level EQ-5D test (EQ5D-5L), the 12-item WHO Disability Assessment Schedule (WHODAS), the Montreal Cognitive Assessment (MOCA), the Hospital Anxiety and Depression Scale (HADS-A/D), and a screening tool named PCL-5 for Post-Traumatic Stress Disorder (PTSD). If patients are unable to attend the post-COVID-19 clinic, the questionnaires will be able to be completed through a phone interview. All questionnaires will be standardized and available in multiple languages (Fig. 1).

Further instrumental diagnostic evaluations such as diffusing capacity of lung carbon monoxide (DLCO), spirometry, lung computed tomography (CT) scans, pneumological evaluation, echocardiography, cardiological evaluation, neurological evaluation, rehabilitation medicine specialist examination, and psychological evaluation will be conducted as necessary.

Pulmonary symptoms are common after the acute phase, thus patients undergo the MRC dyspnoea scale and oxygen saturation measurement at each post-COVID visit. Further evaluations such as chest CT scans, diffusing capacity of lung carbon monoxide (DLCO), spirometry, and a complete pneumological evaluation will be performed if oxygen saturation is < 95% or MRC dyspnoea scale grade is 2–5.

Patients who recovered from acute COVID-19 disease could present a higher risk of cardiac diseases, including heart failure, myocardial infarction, and arrhythmia in the mid- and long-term [18]. During the scheduled post-COVID visits, patients undergo a complete medical examination, including heart rate and blood pressure measurement, and fill in the MRC dyspnoea scale. Further evaluations such as an electrocardiogram, a cardiologic visit, and an echocardiography will be performed as necessary.

Neurocognitive and neuropsychiatric sequelae are important to investigate for their great impact on patients’ quality of life [6, 19, 20]. Neurocognitive and neuropsychological performance will be assessed by questionnaires, including the previously mentioned HADS-A/D, PCL-5, and MOCA, which will be performed at each scheduled visit. Patients will be referred to a psychologist or a neurologist as necessary (Table 1).

**Table 1 Tab1:** Displaying the specific assessments to be conducted at each study time point

Study Flowchart				
**Procedures**	**At acute phase**	**At T1 (2–3 months)**	**At T2 (6–9 months)**	**At T3 (12–15 months)**
Nasopharyngeal swab	X			
Demographic/clinical data collection	X			
Routine blood tests		X	X	X
Blood/serum samples collection		X	X	X
Medical visit, oxygen saturation (SO2) measurement		X	X	X
Symptoms assessment (WHO CRF)		X	X	X
Fatigue Numerical Rating and Severity Scale		X	X	X
Modified MRC Dyspnoea Scale		X	X	X
Hospital re-admission, relapse or new comorbidity		X	X	X
COVID-19 vaccination status		X	X	X
QoL (EQ5D-5L)		X	X	X
Montreal Cognitive Assessment (MOCA)		X	X	X
Psychological questionnaires (HADS-A/D, PCL-5)		X	X	X
WHODAS questionnaire		X	X	X
If abnormal SO2, DLCO		X		X
If abnormal SO2, spirometry		X		X
If abnormal SO2 and/or clinically indicated, pneumology visit		X	X	X
Electrocardiogram (ECG)		X		
If cardiac symptoms, echocardiogram		X		X
If cardiac symptom and/or clinically indicated, cardiology visit		X	X	X
If abnormal psychological questionnaires and/or clinically indicated, psychology evaluation		X	X	X
If abnormally MOCA and/or clinically indicated, neurology visit		X	X	X
If abnormally WHODAS and/or clinically indicated, rehabilitation medicine visit		X	X	X

Legend: T1, T2 and T3: post COVID-19 visit at 2-3 months, 6-9 months and 12-15 months after clinical recovery.

Blood/serum samples collection: whole blood samples will be stored, centrifuged, and separated into plasma and peripheral blood mononuclear cells for immunological and viral analyses

WHO CRF, WHO’s Post COVID case report form; MRC dyspnoea scale, Modified Medical Research Council Dyspnoea Scale; QoL (EQ5D-5L), quality of life (5-level EQ-5D version); MOCA, Montreal Cognitive Assessment; HADS-A/D, Hospital Anxiety and Depression Scale; PCL-5, Post Traumatic Stress Disorders (PTSD) checklist for DSM-5; WHODAS, World Health Organization Disability Assessment schedule 2.0, 12-item version; DLCO, Diffusing capacity of the lung for carbon monoxide test

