### Questionnaires administration

The fatigue numerical rating scale will be used to assess the severity of fatigue experienced by patients, while the MRC dyspnoea scale will be used to evaluate breathlessness. Quality of life will be assessed using the EQ5D-5L tool, which consists of the EQ-5D descriptive system and the EQ visual analogue scale (EQ-VAS). The HADS will be used to evaluate symptoms of anxiety and depression, while the PCL-5 will be used for first screening for PTSD and monitoring symptoms change during time. The MOCA will be used to assess cognitive function, and the WHODAS 2.0 will be used to measure health and disabilities in clinical practice. All questionnaires with the relative scores and the CRF will be listed in Table 2 and more detailed information attached as supplementary documents (Supplementary Appendix).

**Table 2 Tab2:** Presenting the questionnaires administered to enrolled patients, along with information regarding their scoring

Administered questionnaires	
**Score**	**Levels/range**
Symptom assessment with COVID-19 WHO CRF	-Yes, but not present anymore
	-Yes, still present
	-Yes, intermittent
	-No
	-Unknown
Fatigue Numerical Rating Scale Fatigue Severity Scale	Likert Scale from 1 to 7
	Likert Scale from 0 to 10
Modified Medical Research Council (MRC) Dyspnoea Scale	Likert Scale from 0 to 4
Comorbidity relapse or new comorbidity	-Yes
	-No
	-If yes, type of comorbidity and date of diagnosis
Hospital re-admission	-Yes
	-No
	-If yes, reason and date of re-admission
QoL (EQ5D-5L)	Likert scale from 1 to 5
	Scale from 0 to 100
Hospital Anxiety and Depression Scale (HADS-A/D)	Score Depression from 0 to 21
	Score Anxiety from 0 to 21
	(0–7 normal, 8–10 borderline, 11–21 patological)
Post Traumatic Stress Disorders (PTSD) checklist for DSM-5 (PCL-5)	Score from 0 to 80
Montreal Cognitive Assessment (MOCA)	Score from 0 to 30 (adjusted for age and education) (≥ 26 no cognitive impairment; < 26 cognitive impairment
Functioning (WHODAS)	Score from 0 to 100

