The comprehensive questionnaires for symptom collection and the scales for the objective and standardised measure of symptoms such as dyspnoea, fatigue, and psychological issues (anxiety, depression, PTSD, and health-related quality of life) will be repeated at different time points, allowing us to understand the duration and evolution of symptoms over time. Through questionnaires, data about vaccination against SARS CoV-2, reinfections, and new health problems requiring hospital admission or new diagnosis after COVID-19, such as the new onset of diabetes or other health conditions, will be collected.

The collection of biological samples will allow future studies on pathogenetic mechanisms of post-COVID-19 sequelae, such as persistent or excessive inflammation, immune dysregulation, or viral reservoirs.

The strengths of this study protocol are the inclusion of several cohorts outside Europe and the long study period that allows a clear and wide overview of the post COVID-19 condition. We also need to recognise that the study has some limitations, as already stated. Possible solutions to overcome these limitations could be the use of statistical methods such as propensity score matching to address biases due to losses of follow-up. The telehealth approach that is currently being implemented at the coordinating centre for performing post-COVID-19 evaluations without coming to the hospital could reduce losses to follow-up.

In conclusion, the EuCARE-POSTCOVID Study is an international multicentre cohort study that aims to better define and characterise the post COVID-19 condition over the different pandemic waves. The comprehension of the current epidemiology, predictors, clinical manifestations, and pathogenetic mechanisms of this syndrome is crucial in delineating the best management and therapeutic approaches that could improve patients' quality of life.

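### The protocol lets the MOCA be completed by phone but gives it one 0–30 range and one cut-off of 26, so phone and clinic classifications of cognitive impairment are not shown to be comparable

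*Protocol article*

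**What the plan says.** The section on patient assessment and follow-up lists the instruments used at each visit, among them "the Montreal Cognitive Assessment (MOCA), the Hospital Anxiety and Depression Scale (HADS-A/D"). Soon after the list comes the phone permission: "If patients are unable to attend the post-COVID-19 clinic, the questionnaires will be able to be completed through a phone interview". No instrument is excepted. The same section later says that neurocognitive and neuropsychological performance "will be assessed by questionnaires, including the previously mentioned HADS-A/D, PCL-5, and MOCA, which will be performed at each scheduled visit".

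Table 2, under Questionnaires administration, gives the MOCA scoring as "Score from 0 to 30 (adjusted for age and education"), with 26 and above meaning no impairment and anything lower meaning impairment. It gives no phone version, second range or second cut-off. The text refers the reader to "more detailed information attached as supplementary documents (Supplementary Appendix"), which is not among the documents.

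Table 1 attaches a consequence to the score at all three visits: "If abnormally MOCA and/or clinically indicated, neurology visit". Study objectives lists the central nervous system among the organs whose long-term impairment is to be related to age, severity, comorbidities and virology.

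**The concern.** The other scored scales in Table 2 are ratings or self-reports that can be read aloud. The MOCA measures performance. If part of it needs the patient to see or draw, a voice call cannot deliver that part, and a score out of fewer points would be read against a threshold set for 30.

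The MOCA is the only cognitive performance test scheduled in Table 1. A mode effect would therefore enter the cognitive part of the central nervous system objective directly. A patient who moves from clinic to phone between visits could appear to decline, and one who moves the other way could appear to recover. Phone use is not random either, because it is tied to being unable to attend. The inverse probability weighting in Data analysis models which hospitalised patients enter the post-COVID cohort. It does not model how a visit was held, so it would not correct this error.

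**Working it through.** The plan offers no calculated figure to reproduce here; its only figures on this point are the MOCA range (0–30) and the cut-off (26).

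**Step 1: does the phone permission cover the MOCA?** The MOCA is in the list that the permission refers back to, it is called a questionnaire again later in the same section, and Table 2 includes it among the administered questionnaires. On the text as written, it is covered.

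**Step 2: effect on the maximum score.** Let v be the number of points that cannot be obtained by phone and so count as zero. The documents do not give v, so it is varied.

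Phone maximum = 30 − v. With an adjustment of +1 (an assumed size; Table 2 says only that the score is adjusted), it is 31 − v.

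| v | Maximum | Can reach 26? | With +1, can reach 26? |
|---|---|---|---|
| 0 | 30 | yes | yes |
| 4 | 26 | yes | yes |
| 5 | 25 | no | yes |
| 6 | 24 | no | no |
| 8 | 22 | no | no |
| 12 | 18 | no | no |

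For v from 1 to 4, a phone patient who makes no error still passes, but scores shift down. A patient whose full in-person score would lie between 26 and 25 + v falls below 26 by phone if enough of that score came from the lost items. At v = 3 this band is 26 to 28.

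**Step 3: effect on the observed impairment rate when v is 5 or more (no adjustment).** Let t be the true rate by the in-person test and f the share of visits by phone. All phone patients are then classed as impaired:

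observed rate = t(1 − f) + f

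| t | f = 5% | f = 10% | f = 20% | f = 35% |
|---|---|---|---|---|
| 10% | 14.5% | 19% | 28% | 41.5% |
| 20% | 24% | 28% | 36% | 48% |
| 30% | 33.5% | 37% | 44% | 54.5% |

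Both t and f are assumed; the documents give neither.

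**Step 4: effect on an association.** Take t = 25% in both severity groups, so the true odds ratio is 1. Suppose 30% of severe cases and 10% of mild cases are seen by phone (assumed).

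- Severe: 0.25 × 0.70 + 0.30 = 0.475
- Mild: 0.25 × 0.90 + 0.10 = 0.325
- Odds ratio: (0.475/0.525) / (0.325/0.675) = 1.88

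If the phone shares are exchanged, the odds ratio is 1/1.88 = 0.53. The false association can therefore go either way.

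**The case against.** The strongest reply is that the decisive premise lies outside the documents. They do not describe the MOCA items or tell a site to score undelivered items as zero. A site could use a phone version or leave the MOCA missing. The article condenses a fuller protocol and sends questionnaire detail to an appendix that may settle the matter. Table 1 also uses the word questionnaire for the psychological scales and the WHODAS but not for the MOCA, so the permission might not have been meant to cover it. The Discussion's hope that "performing post-COVID-19 evaluations without coming to the hospital could reduce losses to follow-up" mentions neither phone nor MOCA.

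Much of this limits the size of the point. A reader might infer that every phone patient will be classed as impaired whatever their cognition. The documents do not support that: it needs at least 5 lost points (6 with a one-point adjustment), all scored zero. A reader might also infer that the error must exaggerate the link with severity. The limitations section says that patients without ongoing symptoms may be the ones who miss appointments, so well patients could be over-represented among phone visits.

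The central nervous system objective also has neurological symptoms from the WHO form and specialist evaluation, and the neurology visit may follow clinical indication alone.

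What remains is more than a missing detail. The article states a permission that includes the MOCA and a single scoring rule, and together they apply one cut-off to both modes. If the appendix names a shorter phone version, Table 2 would still need to be reconciled with it.

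**Conclusion.** The point holds in a limited form. As written, the protocol permits phone MOCA and supplies only a 0–30 range and a cut-off of 26 to score it. With any v above zero, phone scores run low. With v of 5 or more (6 if one point is added), all phone patients fall below 26 and the observed rate rises from t to t + f(1 − t), for example from 20% to 36% when one visit in five is by phone. These sizes rest on assumed values of v, t and f and on lost items being scored zero; at v = 0 there is no effect.

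The error may be related to severity, symptoms, age or centre, and its direction cannot be settled from the documents. It reaches the cognitive part of one secondary objective and within-patient change. It does not directly reach the primary outcome, which uses the WHO definition, or the sample size, which is built on that outcome. This should be corrected, but it does not threaten the study's main result.

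**What to change.** In the section on patient assessment and follow-up, except the full MOCA from phone completion, or name a phone version with its own range and analyse it as a separate variable. Record the mode of administration at each visit. State in Table 2 that the 0–30 range and the 26 cut-off apply only to full in-person tests.

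In Data analysis, base cognitive impairment and change on full in-person tests. Treat phone-visit MOCA as missing under the multiple imputation option already listed there, with visit mode and the other questionnaires among the predictors, and report a sensitivity analysis by mode. The neurology-visit trigger in Table 1 and the phone permission must also be reconciled.

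The change costs a sentence or two of protocol text, a note to Table 2 and one form field. There are fewer observed MOCA values, and an in-person endpoint depends on attendance, which may itself be related to severity, symptoms, age and centre. Imputation addresses that only as far as the recorded predictors explain who attends, so the dependence should be stated when results are reported. For visits already held, mode would have to be recovered from site records where possible.
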